Today, there is growing evidence that self-report measures are sensitive and reliable tools to monitor athletes’ health [22, 37, 38]. For example, Jacobsson and co-workers [33] reported the development of a web-based self-report system for the Swedish Athletics study. They found that to allow specific analyses of overuse injuries, recording of partial time-loss injuries and regular collection of self-reported data over time was necessary in order to find searches for complex aetiological patterns. It is well-known that many injury-related musculoskeletal incidents result from the cumulative effects of smaller amplitude of micro-traumatic forces developing over time [39]. Therefore, to prevent injuries and overuse problems to develop into chronic conditions, it is useful to have self-report data that highlights the small and early decrements in functioning [40]. Also, data on other medical conditions, such as illnesses, training availability and training load, are important to allow us to understand health conditions beyond injuries [41, 42]. For example, loss of training time due to a health problem has recently been proposed to be a major determinant of success and failure [42]. Recent research in able-bodied athletes also indicates that a high chronic workload seems to decrease the risk of injuries, whereas excessive and rapid increases in training loads are likely to cause a large proportion of injuries [43].

With a systematic longitudinal self-report surveillance system based on exposure it would be possible to observe trends and risk factors of sports-related injuries and illnesses in Paralympic sport and thereby have a basis for the development of specific preventive measures. However, for injury surveillance data to be useful for prevention, a theoretical framework is required to understand how factors representative of the target population influence injuries and illnesses [44]. Moreover, to improve reach, implementation and maintenance it has been recommended that surveillance systems are user friendly and accessible in a wide range of form [45], in this case adapted for persons with physical, visual or intellectual impairments. To capture all sports-related injuries and illnesses in Paralympic sport, to obtain valid data and to allow specific injury prevention measures, there is a need for injury surveillance systems to be specifically tailored to Paralympic sport, targeting a wide range of para-athletes.

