## Purpose

The purpose here is to present a protocol for a prospective longitudinal study: The Sports-Related Injuries and Illnesses in Paralympic Sport Study (SRIIPSS). In this study we will develop a web-based system that allows self-report data to be collected from Paralympic athletes. Based on these data, we will subsequently: i) record and prospectively estimate the annual incidence of sports-related injuries and illnesses among Swedish Paralympic athletes and ii) explore risk factors and mechanisms for sustaining sports-related injuries and illnesses based on athlete exposure and training loads.

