### Setting and participants

Potential participants will be recruited through the Swedish Paralympic Program, which covers candidates for the Summer and Winter Paralympic Games. The total number of athletes in the Swedish Paralympic program is around 100. All potential participants will be invited by post or email. They will receive information about the proposed study, a request for a contact e-mail and phone number, a consent form for participation and a prepaid return envelope. To be eligible for the study the athlete should belong to one of the ten eligible impairment types, according to the IPC classification system, and participate in either a Paralympic summer or winter sport (Table 1). The following inclusion criteria will be used: age 18–55 years, being a registered athlete within the Swedish Paralympic Program, being able to communicate in Swedish and having the opportunity to respond weekly to a web-based questionnaire. As the number of Swedish Paralympic athletes is small and this is an understudied topic, a total population design will be applied.

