### Protocol implementation

The SRIIPSS will employ approaches similar to those that have been used in previous sports injury research [9, 23, 30, 33, 52]. It is, however, hypothesized that sports-related injuries and illnesses among Paralympic athletes differ from sport for able-bodied athletes [13, 15]. Existing research has shown that the accessibility, compatibility, interface and design of questions influence the outcome of athletes’ self-report measures [38]. Therefore, we will specifically adapt the protocol to Paralympic sport and thereafter implement the data collection.

For the data recording a commercial product for collection of survey data online (Briteback AB, Norrköping, Sweden; www.briteback.com) will be used. The research team participates in the development of the system to specifically adapt it to, for example, visually impaired athletes. The product enables definition of personal usernames and passwords to protect data from unauthorised use.

A pilot study is planned where we will enroll approximately twenty athletes with different impairments through a convenience sample from the Swedish Paralympic Program. The pilot study aims to evaluate the feasibility of the data collection system, to assure that it works for athletes with physical, visual and intellectual impairments, and to recognize and solve potential problems. The athletes will be asked to fill in the survey during 4 weeks. The pilot study period will end with a cognitive walkthrough to review the primary protocol and also validate the data. This is an evaluation method that aims to assess usability problems of a new tool early in the design process [53]. The athletes and researchers will be asked to evaluate and provide solutions for the proposed system.

Data will be collected from the end of 2016 and continue for approximately 1 year. At the start of the study the athletes fill in baseline information and a psychological profile. The athletes will thereafter be asked to report sports-related injuries and illnesses weekly. The primary outcome of the study is the incidence of injuries and illnesses, divided into a sports-related injury or illness. All data will be based on sport exposure and analyzed for the mechanism of sports-related injuries and illnesses. A closure form will be used when the athlete is back in full training following an injury or illness (Table 2).

**Table 2 Tab2:** Overview of the outcome measures of the SRIIPSS

Outcome measure	Parameter	Measurement

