### Athlete weekly e-diary

To collect data on new sports-related injuries and illnesses as well as on exposure, the athletes will be asked to fill in a weekly e-dairy based on one developed by Jacobsson et al. [33] and adapted for Paralympic sport. Each week, an alert is automatically sent to the participants’ email address and mobile phone, asking them to fill in the weekly questionnaire about their current health status (injuries, illnesses and pain), the amount of training, intensity of training, whether the training is performed at full capacity, competitions, sleep, general well-being and medical contacts. In addition, anxiety/depression and pain/discomfort will be evaluated using two questions from EQ-5D [61].

If the athlete reports a new injury or illness in their weekly e-dairy, a link to an injury or illness report form will be provided, where additional information on the incident are to be reported. The study coordinator (KF) monitors the reported data. If a participant is absent from training because of an undiagnosed injury or illness lasting longer than 3 weeks, the participant will be contacted by phone or email. The athletes will be asked to go through an examination by a sports physician or sports physiotherapist to confirm the clinical diagnosis, in order to validate the data.

Internal training loads will be recorded based on a modified version from Gabbett & Jenkins [62] and Foster et al. [63]. The athletes will be asked to estimate their total rating of perceived exertion (RPE) during the past week on a 0–10 point RPE-scale [62]. Previous research has demonstrated that the RPE method is a valid method to quantify exercise training during a wide variety of exercise types [63], and the method has also been shown to provide valid estimates when compared to heart rate and blood lactate concentration. The training load will be calculated by multiplying the training session intensity with the duration of the training during the week and will be further analysed with the relationship of injury/illness, acute loads and chronic loads [43, 62, 64].

Assistance will be provided, if necessary, for athletes with vision or intellectual impairment, or severe physical impairment. At the start of the study the athletes will be educated about the importance of monitoring. Feedback will be given, if desired, to allow data to be used to the athletes’ benefit.

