### Statistical analysis plan

The primary variables for the descriptive analyses are records of the incidence of sports-related injuries and illnesses, i.e., recordings of injury or illness events that are conditioned on that the participant is ‘healthy’ at the start of data collection period. Incidences will be calculated separately for injuries and illnesses. The incidence rates will be calculated as the number of new incidents divided by total athlete exposure hours (per 1000 h of sport participation). Health-incidents not related to sport will be analyzed separately. All events will be evaluated according to the mechanism of sports-related injuries and illnesses (independent variables). The data will be assessed for normality and will be presented using quantitative descriptive statistics (mean, median, standard deviation, minimum and maximum for continuous data and frequency and proportion (%) for categorical data). Differences in proportions between different categories (e.g., age-groups, gender, impairments, previous injury, competition frequency and level of severity of impairment) will be analyzed as covariates using chi-square statistics. The primary end point for the injury risk analyses will be time to injury. The incidence data will be further analyzed with the Kaplan-Meier survival analysis method, the log-rank test and Cox proportional hazards regression. To analyze the relationship between training loads and injury and illness incidence, Pearson product moment correlation coefficients will be used. A significance level of 0.05 and 95 % confidence intervals will be used in all tests. The data will be analyzed using IBM SPSS Statistics version 23.

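### Pearson correlation is the only method named for training load against injury and illness incidence, and neither natural unit of analysis gives it a sound answer

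*Protocol article*

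**What the plan says.** The second aim is to "explore risk factors and mechanisms for sustaining sports-related injuries and illnesses based on athlete exposure and training loads" (Purpose). About 100 athletes are expected ("The total number of athletes in the Swedish Paralympic program is around 100", Setting and participants), followed for about a year with weekly reports: "The athletes will thereafter be asked to report sports-related injuries and illnesses weekly" (Protocol implementation).

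Load is built each week: "The training load will be calculated by multiplying the training session intensity with the duration of the training during the week" (Athlete weekly e-diary). That section adds that load will be examined in relation to injury, illness, acute load and chronic load, but names no model.

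The Statistical analysis plan section names one: "To analyze the relationship between training loads and injury and illness incidence, Pearson product moment correlation coefficients will be used". It also says "A significance level of 0.05 and 95 % confidence intervals will be used in all tests", so the coefficient will be tested. The same section divides incidence by exposure hours. It plans Kaplan-Meier, log-rank and Cox analyses for the incidence data, without naming load as a covariate.

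Two other places matter. Definitions of injury and illness makes an event recordable only if it alters the mode, duration, intensity or frequency of training or competition. Athlete monitoring in Paralympic sport gives the expected pattern: a "high chronic workload seems to decrease the risk of injuries, whereas excessive and rapid increases in training loads are likely to cause" a large share of injuries.

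**The concern.** The method is stated, so this is not a detail left to a fuller document. Four features of the protocol's own design work against it.

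- **Repeated weeks.** Up to about 100 x 52 = 5,200 athlete-weeks come from about 100 people.
- **Events act on load.** A recordable event changes training, and load is intensity times duration. Without a lag, the outcome can lower the exposure it is correlated with.
- **Shared hours.** Duration is a factor of load, and hours are the denominator of the incidence rate.
- **Two effects of opposite sign.** Chronic load is expected to protect and rapid increases to harm. One coefficient on total load mixes them.

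The first two apply if athlete-weeks are pooled, and the third if each athlete contributes one rate. They are not all present in one analysis, but each natural choice meets at least one. The results are meant to feed preventive measures, so a biased load coefficient could mislead about which training pattern is safe.

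**Working it through.** The protocol gives no event rate, variance or effect size, so there is no figure to reproduce. Unless noted, the checks simulate 100 athletes x 52 weeks. Assumed: hours lognormal around 10 per week with log-scale SD 0.4 between and 0.3 within athletes; RPE mean 5, SD 1 between and 1 within; weekly event risk 0.05. Tests are two-sided at 0.05.

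**1. Athlete-weeks pooled, no true effect, athletes differing in risk.** False-positive rate:

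| Weekly risk | Frailty SD 0 | SD 0.5 | SD 1.0 |
|---|---|---|---|
| 0.02 | 4% | 6% | 14% |
| 0.05 | 5% | 9% | 27% |
| 0.10 | 4% | 16% | 38% |

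With one mean per athlete it stays at 4-6%. Clustering therefore affects p-values and intervals, and only under pooling.

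**2. Athlete-weeks pooled, same-week pairing.** Let p be the weekly risk, c the fraction of load lost in an event week, CV the coefficient of variation of load, and d the true excess load in event weeks, in SDs, before the cut. Then approximately

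r = sqrt(p(1-p)) x [d(1-c) - c/CV].

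Here sqrt(0.05 x 0.95) = 0.218. The log-variance of hours is 0.16 + 0.09 = 0.25 and the squared CV of RPE is 2/25 = 0.08, so CV = sqrt(e^0.25 x 1.08 - 1) = 0.62.

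No true effect (d = 0), c = 0.25: r = -0.25 x 0.218/0.62 = -0.09. Simulation gives -0.09, significantly negative in 100% of runs.

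| True log rate ratio per SD of load | No cut | 25% cut | 50% cut |
|---|---|---|---|
| 0 | 0.00 | -0.09 | -0.18 |
| +0.2 | +0.06 | -0.05 | -0.15 |
| +0.4 | +0.15 | +0.02 | -0.11 |

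The bias is downward throughout. The sign turns when c/(1-c) exceeds d x CV:
- At +0.2, d = 0.059/0.218 = 0.27, so 0.27 x 0.62 = 0.17 and c must exceed about 0.14.
- At +0.4, d = 0.154/0.218 = 0.71, so 0.71 x 0.62 = 0.44 and c must exceed about 0.31.

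A second setting used 80 athletes, 48 weeks, 2 events per athlete-year and risk proportional to hours, with the cut drawn uniformly. For cuts of 0-50% r was about +0.03. For cuts of 0-100% it was about -0.06. Reversal there needs large cuts.

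**3. One value per athlete: rate per 1000 h against mean load.** If expected events are proportional to H^e, where H is hours, the rate is proportional to H^(e-1), while load rises with H. With RPE unrelated to hours, the correlation takes the sign of e - 1.

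| e | Mean r | Significant |
|---|---|---|
| 0 | -0.40 | 99.8% negative |
| 0.5 | -0.23 | 69% negative |
| 1.0 | 0.01 | 4% either way |
| 1.3 | +0.16 | 34% positive |

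At e = 0.5 athletes with more hours have more events, yet r is negative. That is true of the rate per hour, but it is not evidence that load protects.

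**4. The protocol's own pattern, one coefficient on total load.** With chronic load (prior four weeks) at -0.3 and acute change at +0.3 log rate ratio per SD, weekly r is -0.01, significant in 13% of runs. Athlete-mean r is -0.40. With -0.5 and +0.3, weekly r is -0.045, significantly negative in 88%. The harmful acute effect does not show in any of these.

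**The case against.** The strongest reply is that the article fixes neither the unit nor the lag, so the faults depend on choices the investigators may not make. Much of this stands. With one value per athlete the independence problem disappears. Pearson on the preceding week's load kept the right sign in the 80-athlete setting even with cuts of 0-100% (r about +0.05 to +0.06). Athlete-mean load against event count, rather than rate, was also positive there. Separate coefficients for chronic load and acute change recovered both signs (about -0.06 and +0.07), and the e-diary section mentions both quantities. The injury definition also admits events that change only the mode of training and cost no time, so not every event lowers load.

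Four stronger readings are tempting, and the documents do not support them:
- That the plan treats weeks as independent. The unit is not stated.
- That the load effect will come out reversed. This needs same-week pairing and large enough cuts, or rates that rise less than in proportion to hours.
- That the expected relation is U-shaped. The background describes two variables with opposite effects, not a curve in one.
- That ignored clustering causes a null or reversed sign. It distorts p-values and intervals.

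The reply does not rescue the sentence as written. The versions that behave better are not stated, and an ordinary Pearson test on lagged athlete-weeks still ignores clustering. Cox regression is planned, but load is not assigned to it.

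**Conclusion.** The point holds in limited form. Pearson correlation is the only method the article assigns to load. Pooled weeks give false-positive rates of 6-38% instead of 5% when athletes differ in risk (frailty SD 0.5-1.0), and same-week pairing adds a downward bias of about 0.09 at a 25% cut with no true effect. One rate per athlete loses time order and gives r of -0.40 to about 0 as events go from independent of hours to proportional to them. A single total-load coefficient can hide the two effects the background cites.

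The sizes rest on assumed event rates, variances and cuts. The direction of the same-week bias rests on events lowering load on average, which the definition makes likely but not certain. This should be fixed but is not critical: aim ii is exploratory, and the primary outcome, incidence, is untouched.

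**What to change.** Replace the Pearson sentence with a week-level model for a new incident in week t, fitted separately for injury and illness:

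- **Data:** only athlete-weeks at risk, meaning the athlete is not already off full training.
- **Model:** logistic GEE or random intercept per athlete; or recurrent-event Cox with time-varying load and robust variance.
- **Load:** only from weeks before t, in two terms: chronic load (rolling mean of prior weeks) and acute change or the acute:chronic ratio. Acute, chronic and their difference must not be entered together, because they are exactly collinear.
- **Offset:** if one is wanted, use prior-week or usual hours. The event week's hours may be shortened by the event itself.
- **Size of model:** a non-linear term only if events permit, and few covariates, such as previous injury. At weekly risks of 0.02 to 0.10, 5,200 athlete-weeks give about 104 to 520 events, fewer with dropout or missed reports.
- **Reporting:** odds, rate or hazard ratios with athlete-clustered 95% confidence intervals. Pearson r may stay as a descriptive figure.

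The weekly load, incident and closure data are already planned, so collection does not change. The cost is slightly more analysis work and the loss of each athlete's first few weeks while the chronic window fills.

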## Discussion

We here present a protocol for a prospective epidemiological study of sports-related injuries and illnesses in Paralympic sport and provide arguments related to its design. To the best of our knowledge, no study has prospectively and comprehensively assessed the epidemiology of sports-related injuries and illnesses in Paralympic sport over a longer period of time. Health related problems, in particular musculoskeletal injuries, are common in sport [10]. Previous studies have indicated that sports-related injuries and illnesses is a major concern also within Paralympic sport [23, 24]. Moreover, few studies have analyzed the onset and diagnosis of sports-related injuries and illnesses and further analyzed impairment-related and sport specific risk factors. The proposed study protocol will be used to assess injures and illnesses over time and between different sports and populations. With sports-related injuries and illnesses incident cause data based on athlete exposure it will be possible to observe trends, potential interactions and risk factors over time, and thereby target sports with a higher risk.

It could be argued that a limitation is that no data on clinical examinations are included at baseline. However, self-report systems have previously been shown to enable valid and reliable recordings of sports-related incidents [67] and to monitor changes in athletes’ well-being [68]. This longitudinal research project covers a complex and understudied field. To move forward, basic and feasible research is required. In particular, long-term analyses of possible cause-relationships of sports-related injuries and illnesses by athlete classification and specific impairment type are of importance, as it is hypothesized that injuries and illnesses may be specific for athletes’ sport and impairment type [14]. Other challenges that long-term self-report studies may face are drop-out of participants, low response rates, and problems understanding and interpreting the questions. Moreover, this is the first study among Paralympic athletes with various physical, visual, and intellectual impairments, which requires that the proposed system work for all types of impairments.

The SRIIPSS is expected to lead to an in-depth understanding of the epidemiology of sports-related injuries and illnesses. The results will eventually contribute to the development of evidence-based preventive measures specifically adapted to Paralympic sport in order to provide safe and healthy sport participation. Thereby, the project will be of relevance for Paralympic athletes at all levels and to the Paralympic Movement.

## Abbreviations

BCS: Body consciousness scale
CtESm: Commitment to exercise scale
DSM-IV: Diagnostic and statistical manual of mental disorders
ICD: The International Classification of Diseases
IOC: International Olympic Committee
IPC: International Paralympic Committee
PMCSQ: The Perceived Motivational Climate in Sport Questionnaire
RPE: Rating of perceived exertion
SIC: Subsequent injury categorization
SRIIPSS: The Sports-Related Injuries and Illnesses in Paralympic Sport Study
